## 5. MEASUREMENTS

### 5.1. Blood, urine and CSF sampling (see Appendix 2)

*Blood* will be drawn for the following measurements:

*Screening/ safety:* HbA1c, haemoglobin, leucocytes, thrombocytes, creatinine, liver enzymes (AF,  $\gamma$ -GT, ALT), TSH, lipid profile

*Study parameters:* glucose, insulin (specific assays), albumin, leptin, ghrelin

*Exploratory variables:* advanced glycation endproducts (AGE's, in particular Nε-(carboxymethyl)-lysine (CML), Nε-(carboxyethyl)-lysine (CEL) and 3-deoxyglucosone (3DG)), markers of oxidative stress (Malondialdehyde, Ox-LDL) and inflammation (IL6/TNF $\alpha$ /CRPs), ketone bodies, lactate, APOE genotype and MBL (mannose-binding lectin)

*Cerebrospinal fluid (CSF)* will be obtained to measure:

*Safety/ standardisation:* total cells, total protein

*Study parameters:* glucose, insulin (specific parameters), albumin

*Exploratory variables:* A $\beta$ 42, tau, p-tau, and AGE's (CEL, CML, 3DG)

*Urine:* a 24-hr urine collection will be obtained:

*Screening/ safety:* microalbumin, creatinin

*Exploratory variable:* F2-isoprostanes (oxidative stress)

| InCEREBRO                                                                            |                  |                   |           |              |            |                |            |              |            |                |
|--------------------------------------------------------------------------------------|------------------|-------------------|-----------|--------------|------------|----------------|------------|--------------|------------|----------------|
| Flow Chart                                                                           | Visits           |                   |           |              |            |                |            |              |            |                |
|                                                                                      | 1                | 2                 | TC1       | 3            | 4          |                | TC2        | 5            | 6          | E              |
|                                                                                      | Screening        | Randomi
sation | Tel call  | Measurements |            | Cross-
over | Tel call   | Measurements |            | Evalua
tion |
|                                                                                      | Week
-4       | Week
0         | Week
2 | Week
12   | Week
12 |                | Week
14 | Week
24   | Week
24 | Week
26     |
|                                                                                      |                  | Detemir           |           |              |            | NPH            |            |              |            |                |
|                                                                                      |                  | NPH               |           |              |            | Detemir        |            |              |            |                |
| Informed Consent                                                                     | X                |                   |           |              |            |                |            |              |            |                |
| Incl./Excl. Criteria/ demography                                                     | X                |                   |           |              |            |                |            |              |            |                |
| Start of study insulin                                                               |                  | X                 |           |              |            | X              |            |              |            |                |
| Insulin Therapy (e.g. titration,
instruction, monitoring
hypoglycaemic events) | X                | X                 | X         | X            | X          |                | X          | X            | X          | X              |
| Patient History
- past
- recent                                                | X                | X                 | X         | X            | X          |                | X          | X            | X          |                |
| Physical Examination
- General
- DSP
- Ewing test
- Fundoscopy           | X
X
X
X |                   |           | X            |            |                |            | X            |            |                |
| Vital Signs (incl. body wt)                                                          | X                | X                 |           | X            | X          |                |            | X            | X          | X              |
| Monitoring (S) AE's                                                                  |                  |                   | X         | X            | X          |                | X          | X            | X          |                |
| Concomitant medication                                                               | X                | X                 | X         | X            | X          |                | X          | X            | X          | X              |
| PET-scan                                                                             |                  |                   |           | X            |            |                |            | X            |            |                |
| fMRI-scan                                                                            |                  |                   |           |              | X          |                |            |              | X          |                |
| Blood measurements
- screening
- safety; study parameters                      | X                | X                 |           | X            | X          |                |            | X            | X          |                |
| Lumbar puncture                                                                      |                  |                   |           |              | X          |                |            |              | X          |                |
| Questionnaires:
EDI-II; CES-D
POMS, Likert
DEBQ                             | X                | X                 |           | X
X       | X          |                |            | X
X       | X          |                |
| Urine analysis                                                                       |                  | X                 |           | X            |            |                |            | X            |            |                |

At visit 3 and 4, both in the last week of the assigned treatment, participants will visit our institution in the early morning after an overnight fast from 10 PM. In the evening preceding these visits, patients will inject their dose of insulin detemir or NPH subcutaneously, just as they have done the preceding weeks. Telephone calls will be made to instruct patients what insulin dose to use in order to optimize their blood glucose. Approximately nine hours following the evening injection of the basal insulin (detemir or NPH), PET scanning/fMRI scanning will be performed. Morning (prandial) insulin injection will be administered after fMRI and PET scanning. Blood and CSF samples (lumbar puncture) will be taken (at visit 4 and 6) after MRI scanning.

CSF will be obtained by a lumbar puncture. Patients will be placed in a lateral decubitus position. A 25G atraumatic spinal needle will be inserted, and approximately 10 ml of CSF will be collected. Because this very thin needle will be used, the risk of post-punctional headache is very small [72, 94]; however, patients will be informed about this risk.

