### *Functional MRI (fMRI)*

During the fasting state, the effects of food-related and non-food-related stimuli on brain activation, and the effect of fasting on cognitive performance (memory), will be investigated, comparing both study insulins. Patients will be instructed about the scanning procedure, so they know what to expect. They will however not be aware of the food-related nature of the experiment prior to viewing of the stimuli in the scanner.

The fMRI will start with a resting state (RS) measurement. The following study design will be used [103-106]; in short, a series of food-related as well as non-food-related visual stimuli will be presented via a computer and back-projected onto a translucent screen, visible for the patients via a mirror. A two-button system will be applied to the patients' right hand. The volunteers will be asked to press the left button when the picture is taken "inside" or the right button when it is taken "outside"; this is to test the level of concentration, and to test whether this depends on the nature of the pictures (food-related versus non-food-related) that are shown. After this 'encoding' part of the experiment, ASL measurements will be made, which will take about 8 minutes. Then, a second series of pictures will be shown, using all pictures of the first series mixed with the same number of new pictures. The volunteers will be asked to press the left button when a new picture is seen or the right button when an old picture is recognised ('retrieval' part of the experiment). Correct answers will not be given.

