#### **Appendix 4: Healthy controls**

This INcEREBRO-protocol was designed to investigate whether there are differences between diabetic patients on detemir or NPH insulin in brain regions controlling appetite and satiety – as measured by PET and fMRI –which could explain the differences in weight gain observed in several clinical trials. Because peripheral metabolic signals (a.o. glucose, insulin, free fatty acids, leptin, ghrelin...), known to regulate energy metabolism, satiety and food controlling behaviour via a negative feedback system in the central nervous system are different in diabetic patients as compared to healthy persons, it would be interesting to also compare the studied diabetic patients with age- and BMI-matched healthy controls. Therefore, about 30 healthy volunteers will be included in the protocol. They will have a short screening visit (including informed consent taking, medical history, a physical examination and a screening list to exclude eating disorders, and blood drawing for fasting glucose, liver, renal and thyroid function to make sure they are healthy), after which they will be scheduled for an MRI and a PET scan. Like all patients, all volunteers will be scanned early in the morning in a fasting state. Just before the scans, spare blood will be drawn to measure a.o. glucose, insulin, leptin and ghrelin levels. Before and after scanning, they will fill out the 10-point Likert VAS scale and the POMS mood questionnaire.

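### At the MRI visits patients' blood is taken after scanning and healthy controls' just before it, so the add-on comparison of glucose, insulin, leptin and ghrelin is confounded with sampling point

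*Protocol*

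**What the plan says.** For patients at the MRI visits, Section 5.1 reads: "Blood and CSF samples (lumbar puncture) will be taken (at visit 4 and 6) after MRI scanning". They arrive "in the early morning after an overnight fast from 10 PM". The preceding sentence in the same section adds: "Morning (prandial) insulin injection will be administered after fMRI and PET scanning". The study-parameter list for blood in 5.1 is "glucose, insulin (specific assays), albumin, leptin, ghrelin".

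Section 5.3 describes the session that comes before this sample. In it, "a series of food-related as well as non-food-related visual stimuli will be presented via a computer", first for encoding and later, mixed with new pictures, for retrieval. The MRI summary gives a total of 43 minutes at week 12 and 44 minutes at week 24.

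For the roughly 30 healthy volunteers, Appendix 4 says: "Like all patients, all volunteers will be scanned early in the morning in a fasting state". It continues: "Just before the scans, spare blood will be drawn to measure a.o. glucose, insulin, leptin and ghrelin levels". The reason given for adding them is that peripheral metabolic signals differ between diabetic and healthy people, so that "it would be interesting to also compare the studied diabetic patients with age- and BMI-matched healthy controls".

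Appendix 2 schedules patients' glucose, insulin and albumin at visits 3 and 5 (PET) and at visits 4 and 6 (lumbar puncture), without a time relative to the scan. It has no row for leptin or ghrelin.

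**The concern.** The controls were added to compare circulating signals and the brain response to them between patients and healthy people. For that, blood should be taken at the same point of the visit in both groups. As written, the two groups are sampled on opposite sides of the MRI session. A difference in glucose, insulin, leptin or ghrelin at the MRI visit would then mix the effect of diabetes with any change in these values across the session.

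This follows from complying with the protocol, so a later analysis plan cannot remove it. The protocol treats timing as important elsewhere: Sections 5.2 and 5.3 hold the time of day of all scans constant to limit diurnal variation.

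A smaller point concerns patients alone. Section 5.1 places both the blood/CSF sample and the morning prandial insulin after scanning and does not say which comes first. CSF insulin is secondary endpoint I, and the plasma sample taken with it should have a defined relation to that injection.

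**Working it through.** No alpha, power or sample-size figure is involved. The check sets the sections side by side and adds simple timing and volume arithmetic.

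**1. The two sampling rules**

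| Item | Patients, visits 4 and 6 | Healthy controls |
|---|---|---|
| State on arrival | fasting, early morning (5.1, 5.3) | fasting, early morning (Appendix 4) |
| Blood sample | after the MRI (5.1) | just before the scans (Appendix 4) |
| Food pictures seen before the sample | yes (5.3) | no |
| 5% glucose infusion if needed | possible before and after testing (5.3) | not mentioned |
| Leptin and ghrelin | listed in 5.1, no row in Appendix 2 | drawn before the scans |

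The controls' sample is read here as preceding the MRI. Appendix 4 speaks of the scans in general and does not say whether there is one draw or one per scan.

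**2. Size of the offset**

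A control is drawn at or before scan start and a patient at or after scan end, so the offset relative to scan start is at least the session length: 43 min at visit 4 and 44 min at visit 6. Set-up and the lumbar puncture add time that is not stated.

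Section 5.1 starts scanning about 9 h after the evening basal injection. The patients' sample therefore falls no earlier than about 9 h + 43 min = 9 h 43 min (visit 4) or 9 h + 44 min = 9 h 44 min (visit 6) after it.

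**3. What the comparison would estimate**

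Let P be the patient mean and C the control mean.

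P(after) − C(before) = [P(before) − C(before)] + [P(after) − P(before)]

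The first bracket is the intended contrast. The second is the change in patients across the session. At these visits every patient is sampled after and every control before, so there is no overlap from which to estimate the second bracket. A covariate cannot separate it, and more participants would not reduce it. For glucose there is a partial handle, because Section 5.3 has a finger-prick check before and after testing. For insulin, leptin and ghrelin there is none.

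**4. Whether the PET visits help**

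The after-MRI sentence covers only visits 4 and 6. Glucose and insulin at visits 3 and 5 could therefore be drawn before the scan, and the arterial cannula is in place by then (5.2). But no time is given. Appendix 2 does not place leptin or ghrelin at any visit; the flow chart marks study-parameter blood at visits 3 to 6 without naming analytes.

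The blood budget in Section 10 reproduces: 10 + 3 + 400 + 500 = 913 ml. It gives visits 3 and 5 nothing beyond the PET maximum of 250 ml each. Continuous PET withdrawal takes up to 10 × 5 = 50 ml for water and 10 × 5 + 50 × 2.5 = 175 ml for FDG, together 225 ml. That leaves 250 − 225 = 25 ml for calibration samples and everything else, against up to 200 ml at each of visits 4 and 6. This suggests, without proving it, that most laboratory blood is meant for the post-MRI draw.

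**5. The randomised comparison**

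Section 4.5 repeats the same procedures in the second period. Both insulins are sampled after the MRI, so the patient-control mismatch does not enter the detemir-NPH contrast.

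**6. Sample and prandial insulin**

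Both sentences of Section 5.1 say only that the event follows scanning. Either order complies.

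**The case against.** The strongest reply is that these are two rules for two groups and both can be followed in full. Blood taken with the lumbar puncture has a clear purpose, because it pairs plasma with CSF insulin. Patients also have glucose and insulin at the PET visits, where a pre-scan draw is possible. The control comparison is an addition with no endpoint, hypothesis or sample size of its own, leptin and ghrelin are exploratory variables in Section 3.2, and injected insulin differs from endogenous insulin for reasons far larger than a 43-minute offset.

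Much of this stands. The rules do not contradict each other, the paired sample is worth keeping, and the stakes are modest. It does not answer the mismatch itself. The PET-visit samples rescue glucose and insulin only if their time is fixed, and they do nothing for leptin and ghrelin until those are given a visit.

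Some stronger readings are tempting but not supported:

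- A reader might infer that patients' samples are not fasting. Patients fast from 10 PM and no meal is scheduled before sampling. What the text leaves open is a preceding prandial injection or a 5% glucose infusion.
- A reader might infer that the order of sample and injection drifts between visits 4 and 6. Section 4.5 says procedures are repeated; the order is unstated, not shown to vary.
- A reader might infer that food pictures alter leptin or ghrelin, or that aspart is read as basal insulin. The documents give no such effect and no cross-reactivity figure; Section 5.1 says only that the insulin assays are specific.
- A reader might infer harm to the primary endpoints. These are PET measures and do not depend on this sample.

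**Conclusion.** The point holds for the add-on patient-control comparison of glucose, insulin, leptin and ghrelin at the MRI visits. Group is fully confounded with sampling point relative to the scan, for every patient at both visits, with an offset of at least 43 to 44 minutes. The size and direction of the resulting bias cannot be derived, because the documents give no rate of change for any of these analytes across the session.

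The conclusion assumes that the controls' sample precedes the MRI. For glucose and insulin it is softened if the PET-visit samples are drawn before scanning, which is not stated. The PET primary endpoints are untouched, and the mismatch does not enter the randomised comparison.

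The missing order of sample and prandial insulin is a matter of wording to reconcile. Left open, it could add noise to plasma insulin and to its relation with CSF insulin. The change is worth making because it is cheap before data collection and impossible to repair afterwards.

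**What to change.** - In Section 5.1 and Appendix 2, draw the patients' glucose, insulin, leptin and ghrelin tubes just before the scan, as for the controls. If that is impractical, choose another single sampling point and apply it to both groups.
- Add leptin and ghrelin rows to Appendix 2 with a visit. State the time relative to the scan for the samples at visits 3 and 5, and in Appendix 4 state which scan the controls' draw precedes.
- Keep a small insulin, glucose and albumin tube at the lumbar puncture to pair with CSF.
- Reconcile the two sentences of Section 5.1 so that the order of blood, CSF and prandial insulin is explicit and the same at visits 4 and 6. Which order to adopt is for the sponsor and the investigator to settle.
- Record clock times of scan start and end, each sample, the prandial injection and any glucose infusion, for patients and controls as applicable.

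The cost is a few sentences, two table rows, a split draw and one additional small tube at each of visits 4 and 6. No visit is added. Moving tubes from after to before the scan leaves the volume unchanged. Whether the paired tube fits within the 200 ml maximum cannot be checked, because Section 10 gives no breakdown, so that line should be confirmed.

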## 5.2. Protocol PET

After 12 weeks of treatment, patients will visit the Radionuclide Centre (RNC) in the early morning; they will be instructed to be in a fasting state and not to inject their prandial insulin.

Blood glucose values should be maintained at values ranging from 5-10 mmol/l. Therefore, blood glucose values will be checked (and adjusted, if necessary, by the infusion of 5% glucose) before and after testing using a finger prick.

[figure not shown]

All scans will be acquired at the same time of the day to minimise diurnal variations. All patients will receive an indwelling radial artery cannula. This arterial cannula will be inserted under local anaesthetics by an experienced clinician and will be used for blood sampling. In addition, a venous cannula will be inserted, which will be used for tracer injection (and glucose 5% if necessary). Subjects will be transferred to the scanning room and positioned on the scanner bed. They will be made comfortable in a supine position on the scanner table. The head will be fixated to reduce movement artefacts and, using laser beams, positioned within the centre of axial and transaxial field of views, such that the orbito-meatal line is parallel to the detectors.

### Scanning protocol

PET scans will be performed on an ECAT HRRT (High Resolution Research Tomograph) scanner (Siemens/CTI), a dedicated whole-brain and small animal PET scanner, with design features that enable high image spatial resolution combined with high sensitivity; the scanner field of view (FOV) is 312 mm in diameter and 250 mm in axial length. The HRRT is the first commercially available

scanner that utilizes a double layer of LSO/LYSO crystals to achieve photon detection with depth-of-interaction information [95].

First a 10 minutes transmission scan (TS) will be performed in 2D mode using a single photon emitter moving point source. These data will be used to correct the subsequent emission scans for photon attenuation.

Following the transmission scan, 1100 MBq of [ $^{15}\text{O}$ ]H2O will be injected intravenously, simultaneously starting a dynamic emission scan (ES) in 3D mode. This dynamic scan will have a total duration of 10 minutes and will allow to determine cerebral blood flow (CBF), expressed as ml/100mg/min, in specific brain regions associated with appetite regulation. Throughout the scan, arterial blood will be withdrawn continuously at a rate of 5 ml/min, using an on line detection system (Veenstra Instruments, Joure, Netherlands), cross-calibrated against the PET scanner.

Next, 185 MBq of [ $^{18}\text{F}$ ]FDG will be injected intravenously, again simultaneously starting a dynamic emission scan in 3D mode with a total duration of 60 minutes. This allows to determine cerebral metabolic rate of glucose (CMRglu), expressed as  $\mu\text{mol}/100\text{mg}/\text{min}$ , in specific brain regions. Arterial blood will be withdrawn continuously at a rate of 5 ml/min for the first 10 minutes and 2.5 ml/min thereafter. At set times, continuous withdrawal will be interrupted briefly for the collection of blood samples, which will be used to calibrate the on-line detection system and to estimate plasma-to-whole-blood ratios of radioactivity. After each sample, the line will be flushed with heparinised saline. A maximum of 250 ml blood will be withdrawn during an entire PET session. Total scanning time: 80 minutes.

| Treatment 12 w |                                                                                                                                      | Treatment 12 w |                                                                                                                                      |
|----------------|--------------------------------------------------------------------------------------------------------------------------------------|----------------|--------------------------------------------------------------------------------------------------------------------------------------|
| Detemir        |                                                                                                                                      | NPH            |                                                                                                                                      |
| NPH            |                                                                                                                                      | Detemir        |                                                                                                                                      |
|                | PET
2D TS (10')
1100 MBq H 2 O
3D dyn ES (10')
185 MBq FDG
3D dyn ES (60')

Total: 80' |                | PET
2D TS (10')
1100 MBq H 2 O
3D dyn ES (10')
185 MBq FDG
3D dyn ES (60')

Total: 80' |

*Data analysis*

All dynamic scan data will be corrected for decay, scatter, randoms and (measured) photon attenuation and be reconstructed as 256 x 256 matrices. A spatial resolution of less than 3 mm full width at half maximum (FWHM) on the complete field of view (FOV) will be achieved. PET and MRI scans will be co-registered and regions of interest (ROI) will be defined on anatomical structures outlined within the MRI scan. These ROI will be projected onto the [ $^{15}\text{O}$ ]H2O and [ $^{18}\text{F}$ ]FDG scans, thus creating tissue-time activity curves. CBF and CMRglu and glucose extraction fraction will be derived for these ROI using previously described methods [60, 96, 97]. In addition, CBF and CMRglu will be calculated on a voxel-by-voxel basis using a basis function and a Patlak approach, respectively [98-102].

